### Sample size

To calculate the minimally required number of CR clinics participating in the trial, data from a previous trial (concerning the effect of CDS on guideline concordance) was used [7]. Calculations were based on the normal approximation to the binomial distribution, using a type I error risk (alpha) of 5% and 80% power. Also, we assumed that participating clinics will see 350 CR patients, on average, during the study period of 1 year, and that there will be a design effect of 23.0 due to clustering. This is based on an intra-cluster correlation coefficient (ICC) of 0.063, which is the median ICC for process variables found in 21 studies, reported by Campbell et al. [57].

In the previous study [7], CDS increased concordance with guideline-recommended therapeutic decisions for exercise training from 84.7% to 92.6%. To demonstrate a further increase to 97.6% (+5%) in the current study, at least 19 participating clinics (6,712 patients) are required under the assumptions given. For education, the concordance level previously rose from 63.9% to 87.6%. Demonstrating a further increase to 95.1% (+7.5%) requires 14 participating clinics (5,057 patients). For relaxation therapy, the previous study showed an increase from 34.1% to 59.6%, and showing an additional increase to 74.6% (+15%) requires ten participating clinics (3,517 patients). For lifestyle change therapy, finally, no significant effect of CDS was observed in the previous study (57.4% vs. 54.1%). To prove that the current intervention causes an increase from 57.4% to 72.4% (+15%) will also require that 13 clinics (3,632 patients) participate. Based on these results, we aim to include at least 19 CR clinics in our study.

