**Table 1 Tab1:** **Previous studies—improving guideline concordance in the field of CR**

**Study**	**Description of the studies**
I. *Tackling internal barriers: CDS*	To stimulate the implementation of the Dutch CR Guidelines, an EPR with CDS functionalities named CARDSS (cardiac rehabilitation decision support system) was previously developed [5]. After entering patient data, CARDSS provides its users with a patient-specific, guideline-based rehabilitation program, consisting of recommended rehabilitation goals and therapies. The effect of the system was evaluated in a cluster-randomized trial in 21 CR clinics, which showed that the system increased concordance to the CR guideline: CR professionals using the system better adapted the CR therapy to patients’ needs [7]. Data from the same trial however pointed out that there remained to exist a large variation in CR practice across clinics. For instance, the percentage of patients participating in exercise training varied from 41% in one clinic to 100% in another and the percentage of patients participating in education and counseling programs varied from 39% to 96%.
II. *Persisting barriers after introduction of CDS*	After the trial a qualitative study was conducted to investigate which barriers were reduced and which barriers persisted after introduction of the CDS system [8]. Results from semi-structured interviews with 29 CR professionals showed that the system succeeded in overcoming professional knowledge barriers. For instance, professionals were more aware of the need to use objective instruments to assess patients’ needs and of the therapy decision rules as described in the guidelines. However, two remaining barriers for guideline concordance frequently mentioned were organizational and guideline-related barriers; both can be classified as external barriers according to Cabana et al. [9].
III. *Tackling external guideline-related barriers: revision of the guidelines*	To overcome guideline-related barriers, the clinical algorithm for assessing patient needs in CR was revised [23]. We combined patient data collected by CARDSS and input from academic and practical experts. Assessment of patient needs based on clinical judgment was found to be a source of practice variation and was therefore avoided in the revised algorithm by adding several standardized assessment instruments.

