### Randomization and allocation

We will randomly allocate CR clinics (clusters) to one of the both study arms, stratified by the number of patients per month entering the CR program: small (up to 30 patients) versus large (30 patients or more). Allocation is based on randomization with variable block size (two or four), performed with dedicated computer software written in the statistical programming language R (version 2.13.1). To conceal allocation, the software is used to generate a list of unique codes for both strata, where each code corresponds to an allocation (study arm A or B).

Three researchers will be involved in the allocation procedure. When a clinic is willing to participate, the first researcher ([name]) will determine its stratum and communicate that to a second researcher ([name]) (without naming the clinic involved). The second researcher will look up the next unique code on the list for this stratum and pass that code to a third researcher who can determine the study arm, based on the given code. Using this procedure, both the second and third researchers are fully blinded for the allocation of clinics to the study arms during the procedure. The first researcher is not blinded but can however during this procedure not influence the allocation. Due to the characteristics of the intervention, it will not be possible to blind participants or the investigators providing the intervention.

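### The sample size assumes equal clinic sizes and uses normal quantiles for only 10 to 19 clinics, so the stated 80% power is somewhat overstated even at the stated clinic numbers

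*Protocol article*

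**What the plan says.** The Sample size section gives the method ("Calculations were based on the normal approximation to the binomial distribution"), the error rates ("using a type I error risk (alpha) of 5% and 80% power") and the cluster size: "participating clinics will see 350 CR patients, on average, during the study period of 1 year". It then assumes that "there will be a design effect of 23.0 due to clustering", derived from an "intra-cluster correlation coefficient (ICC) of 0.063, which is the median ICC for process variables found in 21 studies". The stated requirements are 19 clinics for exercise training, 14 for education, 10 for relaxation and 13 for lifestyle change, and the target is at least 19. The abstract speaks of 18.

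Randomization and allocation stratifies clinics by monthly intake: "small (up to 30 patients) versus large (30 patients or more". Statistical analysis plans a mixed-effect logistic regression with clinic as random effect and takes the time × arm interaction as the measure of the intervention effect. Table 1 reports, from the group's earlier 21-clinic trial, that participation in exercise training "varied from 41% in one clinic to 100% in another"; for education and counseling the range was 39% to 96%.

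**The concern.** Three features of the calculation make the 80% doubtful.

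- **Clinic size.** The design effect has no term for unequal clinics. Yet the plan expects them: the stratification cut of 30 per month lies almost exactly at the assumed mean of 350/12 = 29.2 per month.
- **Few clusters.** Normal quantiles treat the between-clinic variance as known. With 10 to 19 clinics it is estimated on 8 to 17 degrees of freedom.
- **ICC.** The baseline concordance rates come from the group's own earlier trial, but the ICC is a published median, applied to all four therapies with no range around it. At 350 patients per clinic the ICC supplies about 22 of the 23 units of the design effect.

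If the real power is below the stated figure, a non-significant result could be read as better evidence against the intervention than it is.

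**Working it through.** **Inputs from the Sample size section:** mean cluster size m = 350, ICC = 0.063, alpha 5% (sidedness is not stated; two-sided reproduces the figures), power 80%. No CV of clinic size is given.

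**1. The plan's own figures.** Design effect = 1 + (m − 1) × ICC = 1 + 349 × 0.063 = 22.987, which rounds to 23.0. The two-proportion formula (pooled variance, no continuity correction) gives 292, 220, 153 and 158 patients per arm. Times 22.987 this is 6,712, 5,057, 3,517 and 3,632, the four stated patient numbers. So 23.0 is the equal-size design effect, and its arithmetic is right.

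**2. t in place of z.** Take each stated clinic number at face value as giving 80% with normal quantiles. The noncentrality is then 1.960 + 0.842 = 2.802. Keep that value and refer it to a noncentral t on (clinics − 2) degrees of freedom:

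| Clinics | df | t critical value | Power |
|---|---|---|---|
| 19 | 17 | 2.110 | 75% |
| 14 | 12 | 2.179 | 73% |
| 10 | 8 | 2.306 | 69% |

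This step needs no assumed CV or alternative ICC. The 18 clinics in the abstract (df 16) also give about 75%.

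**3. Unequal clinic sizes, CV assumed.** The usual formula, which weights patients equally, is 1 + [(1 + CV²) × m − 1] × ICC. In a mixed model a clinic's information is roughly proportional to m/(1 + (m − 1) × ICC). For illustrative clinics of 175, 350 and 525 patients this is 14.6, 15.2 and 15.4, so clinics are weighted almost equally. The mixed-model columns average this over gamma-distributed sizes, on a linear-scale approximation. Power is by z, for exercise training, at the patient number that gives 80% with equal sizes:

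| CV | Design effect, usual formula | Power | Design effect, mixed model | Power |
|---|---|---|---|---|
| 0.3 | 25.0 | 77% | 23.1 | 79.9% |
| 0.5 | 28.5 | 71% | 23.3 | 79.6% |
| 0.65 | 32.3 | 66% | 23.6 | 79.1% |
| 0.8 | 37.1 | 60% | 24.0 | 78.4% |

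The loss is 3 to 20 points by the usual formula, but only about 0 to 2 under the planned model.

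**4. Sensitivity to the ICC** (equal sizes, z, same patient number):

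| ICC | Design effect | Power |
|---|---|---|
| 0.04 | 15.0 | 94% |
| 0.063 | 23.0 | 80% |
| 0.08 | 28.9 | 70% |
| 0.10 | 35.9 | 61% |

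**5. A separate, larger error in the same section.** The patient numbers in step 1 match only as numbers per arm, but the section treats them as trial totals. With 19 clinics in all (19 × 350 = 6,650 patients, 3,325 per arm), exercise training has about 50% power by z, even with equal sizes and an ICC of 0.063. Steps 2 to 4 set this aside.

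**The case against.** The strongest reply is that nothing printed is miscalculated, and that two tempting readings go too far.

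**Unequal sizes.** A reader might infer from the usual formula that varying clinic size alone brings power down to 71% or 60%. The documents do not support this. They give no CV, and that formula describes an analysis that weights patients equally, whereas the planned model includes a random clinic effect. This part of the objection stands: those figures are only an upper bound.

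**ICC.** A reader might also infer from Table 1 that the group's own data show an ICC above 0.063. They do not. The ranges are for participation, while the primary outcome is concordance: treating those who should be treated and not treating the rest. Participation can vary with patient mix even when concordance is perfect. Turning a range into an ICC would also need clinic means and sizes that are not given. A published median for process variables is a defensible choice for a process outcome, and an ICC from 21 clinics would itself be imprecise. The direction of any error is unknown. What remains is that power is highly sensitive to this one value, that no range is shown, and that the Table 1 ranges are a reason to check it.

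**Mismatch with the planned test.** A design effect for a simple comparison of proportions does not give the power of a within-clinic time × arm test, with or without corrections. This also stands, and it applies to the plan's 23.0 as much as to the figures above.

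The few-clusters point is not answered by any of this.

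**Conclusion.** The concern holds in a limited form. Taken at face value, the stated clinic numbers give about 75% (19 clinics), 73% (14) and 69% (10) rather than 80%, once the small number of clusters is allowed for. This rests only on a t reference with clinics minus 2 degrees of freedom. Unequal sizes probably cost a further 0 to 2 points, for an assumed CV of 0.3 to 0.8 and clinics weighted as in the mixed model. The ICC makes the stated power uncertain in both directions; it is not evidence that power is too low.

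The main reason why power falls short is the separate per-arm error, which leaves about 50% for exercise training at 19 clinics. The t correction shrinks as clinics are added: with 19 clinics in each arm (36 degrees of freedom), the same noncentrality of 2.802 gives about 78%.

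**What to change.** Redo the power calculation and report it as follows:

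- use t quantiles on clinics minus 2 degrees of freedom;
- state the assumed CV of clinic size, which the intake figures used for stratification can inform, and the weighting assumed;
- show power over a range of ICCs, including a concordance ICC per therapy with its interval from the earlier 21-clinic trial, if obtainable;
- base the calculation on the time × arm analysis that will be run;
- correct the use of per-arm patient numbers as trial totals in the same step;
- restate the power available for each therapy at the planned number of clinics.

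The cost is a recalculation and a less favourable stated power. This point requires no extra clinics and no new data collection.

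### The sample-size figures are per-arm numbers presented as the whole trial; by the plan's own method, 18–19 clinics give about 50% power for exercise training, not 80%

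*Protocol article*

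**What the plan says.** The Sample size section sets out to find the smallest number of clinics for the trial and gives its method: "Calculations were based on the normal approximation to the binomial distribution, using a type I error risk (alpha) of 5% and 80% power". On clinic size it adds: "we assumed that participating clinics will see 350 CR patients, on average, during the study period of 1 year". The design effect is put at 23.0, and its source is given as follows: "This is based on an intra-cluster correlation coefficient (ICC) of 0.063".

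It then gives one requirement per therapy:

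- Exercise training, 92.6% to 97.6%: "at least 19 participating clinics (6,712 patients) are required under the assumptions given".
- Education, 87.6% to 95.1%: 14 clinics, 5,057 patients.
- Relaxation, 59.6% to 74.6%: 10 clinics, 3,517 patients.
- Lifestyle change, 57.4% to 72.4%: 13 clinics, 3,632 patients.

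The section closes with "we aim to include at least 19 CR clinics in our study". The Abstract gives 18 clinics for the trial. None of these figures is labelled as per arm.

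Under Study design, clinics are divided into arms A and B. Each arm receives the intervention for one domain and is the control for the other. Randomization and allocation uses blocks of two or four, so the split is about 1:1. Statistical analysis bases the effect on the difference in change between the arms.

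**The concern.** For any one therapy, about half of the clinics supply intervention patients and half supply controls. A requirement for the trial must therefore cover two arms. The stated patient counts look too small for that, and dividing 6,712 by 350 gives 19.2, the clinic number then used for the whole trial. If the counts are single-arm sizes, the trial has half the patients its own calculation calls for.

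Concordance for these four therapies is the primary outcome, and this calculation is the only justification given for the trial's size. A non-significant result would be judged against a claimed 80% power. If the real figure is nearer 50%, such a result says much less about whether the target difference exists.

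**Working it through.** **Inputs (all from Sample size).** Alpha 5% (sidedness not stated), power 80%, 350 patients per clinic, ICC 0.063, and the four pairs of proportions above.

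**Design effect.** 1 + (350 − 1) × 0.063 = 22.987, stated as 23.0.

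**Reproducing the plan's patient counts.** Size of one arm, pooled variance, no continuity correction, with p̄ = (p₁ + p₂)/2:

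n = [1.960·√(2p̄(1−p̄)) + 0.842·√(p₁(1−p₁) + p₂(1−p₂))]² / (p₂ − p₁)²

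For exercise training, p̄ = 0.951 and n = (0.5983 + 0.2552)² / 0.05² = 291.4, rounded up to 292.

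| Therapy | n, one arm | rounded up | × 22.987 | stated |
|---|---|---|---|---|
| Exercise | 291.4 | 292 | 6,712 | 6,712 |
| Education | 219.3 | 220 | 5,057 | 5,057 |
| Relaxation | 152.8 | 153 | 3,517 | 3,517 |
| Lifestyle | 157.7 | 158 | 3,632 | 3,632 |

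All four agree to the patient, so the stated counts are single-arm sizes from a two-sided test.

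**Could 6,712 be a two-arm total by another formula?** None of the variants tried gives it. Two-arm totals for exercise training are 13,424 (two-sided, pooled), about 13,279 (two-sided, unpooled), 15,217 (two-sided, continuity-corrected), 10,574 (one-sided, pooled), about 10,460 (one-sided, unpooled) and 12,321 (one-sided, continuity-corrected). A one-sample comparison gives about 3,790 two-sided or 2,879 one-sided.

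**From patients to clinics.** 6,712/350 = 19.2, 5,057/350 = 14.4 and 3,517/350 = 10.05. The text states 19, 14 and 10, so the single-arm counts were divided by 350, rounded down, and used as clinics for the whole trial. Lifestyle change does not follow this pattern: 3,632/350 = 10.4, but 13 is stated. That is a separate inconsistency.

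**Corrected totals.** Twice the single-arm count, divided by 350:

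| Therapy | total patients | clinics |
|---|---|---|
| Exercise | 13,424 | 38.4 |
| Education | 10,114 | 28.9 |
| Relaxation | 7,034 | 20.1 |
| Lifestyle | 7,264 | 20.8 |

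**Power by the plan's method.** With K clinics split equally, the effective number per arm is m = (K/2) × 350 / 22.987, which is 137.0 for K = 18 and 144.6 for K = 19. Power is

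Φ{ [(p₂ − p₁)√m − 1.960·√(2p̄(1−p̄))] / √(p₁(1−p₁) + p₂(1−p₂)) }.

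For exercise training with 19 clinics: (0.05 × √144.6 − 0.5983)/0.3032 = 0.01, so power is 50%.

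| Therapy | 18 clinics | 19 clinics | at the clinic number stated for that therapy |
|---|---|---|---|
| Exercise | 48% | 50% | 50% (19) |
| Education | 60% | 62% | 50% (14) |
| Relaxation | 76% | 78% | 50% (10) |
| Lifestyle | 74% | 76% | 60% (13) |

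**Detectable difference.** At 80% power with 18 clinics, the same formula gives about +6.7 points for exercise training, +9.1 for education, +15.8 for relaxation and +16.0 for lifestyle change. For exercise training that means reaching 92.6 + 6.7 = 99.3%.

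**The case against.** The strongest objection is that these power figures belong to the plan's simplified calculation and not to the planned test. Statistical analysis specifies a time-by-arm interaction in a mixed-effects logistic model. That test uses change within clinics over the year, so a cross-sectional design effect does not carry over to it. Its power could be higher or lower and cannot be computed from the stated inputs. This stands as a limit on how the percentages may be described. It does not rescue the 80% claim, because the protocol supports that claim only by the two-proportion calculation.

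The shortfall is also uneven. Relaxation and lifestyle change miss 80% by about 2 to 6 points at 18–19 clinics, while exercise training and education miss it by about 18 to 32. This is correct, and it is why power should be reported per therapy.

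A one-sided test would put relaxation and lifestyle change above 80% (83–86%). It would leave exercise training at 61–63% and education at 72–74%, and it would not reproduce the stated counts.

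The balanced incomplete block design might seem to let every clinic count twice. It does so across therapies, but for a single therapy each clinic is either intervention or control.

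Finally, the 99.3% figure comes from a normal approximation close to 100%, with only about one effective non-concordant patient expected in the intervention arm (137 × 0.007 ≈ 1). It is indicative only.

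**Conclusion.** The concern holds. The four patient counts are single-arm sizes presented as trial totals, and the factor of 2 is missing. By the plan's own method, 18–19 clinics give 48–50% power for exercise training, 60–62% for education, 76–78% for relaxation and 74–76% for lifestyle change. None reaches 80%. Exercise training, whose requirement set the recruitment target, is the worst placed and would need about twice the clinics.

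These figures assume a two-sided 5% test, 350 patients per clinic, an ICC of 0.063, equal arms and the stated target proportions. They describe the calculation in Sample size, not the mixed model. Two features of the plan could lower power further: clinics that fail the end-of-trial data audit are excluded from the analysis, and Strengths and limitations accepts that spill-over between domains may shrink the observed effect.

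**What to change.** In Sample size:

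1. Relabel 6,712, 5,057, 3,517 and 3,632 as patients per arm, and give the totals 13,424, 10,114, 7,034 and 7,264 with the matching clinic numbers (38.4, 28.9, 20.1 and 20.8 before rounding up).
2. Withdraw the statement that 19 clinics give 80% power.
3. For the clinics actually available, report power per therapy or the difference detectable at 80%. Say that these come from the two-proportion calculation with the stated design effect.
4. State that by this method none of the four therapies reaches 80% at the original targets. Exercise training and education are clearly underpowered; relaxation and lifestyle change fall slightly short.
5. State that the test is two-sided, and correct the 13 clinics given for lifestyle change, which does not match 3,632 patients at 350 per clinic.

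The cost is new wording and one recomputed table. No extra clinics are needed, but the stated power becomes less favourable.

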**Methods:**

A multicenter cluster-randomized trial with a balanced incomplete block design will be conducted in 18 Dutch CR clinics using an electronic patient record with CDS at the point of care. The intervention consists of (i) periodic performance feedback on quality indicators for CR and (ii) educational outreach visits to support local multidisciplinary QI teams focussing on systematically improving the care they provide. The intervention is supported by a web-based system which provides an overview of the feedback and facilitates development and monitoring of local QI plans. The primary outcome will be concordance to national CR guidelines with respect to the CR needs assessment and therapy indication procedure. Secondary outcomes are changes in performance of CR clinics as measured by structure, process and outcome indicators, and changes in practice variation on these indicators. We will also conduct a qualitative process evaluation (concept-mapping methodology) to assess experiences from participating CR clinics and to gain insight into factors which influence the implementation of the intervention.

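### The article gives two trial sizes (18 and at least 19 clinics), and its 13 clinics for lifestyle therapy follow neither from its own patient number nor from twice that number

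*Protocol article*

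**What the plan says.** The Methods paragraph of the abstract says the trial "will be conducted in 18 Dutch CR clinics". The Sample size section, after going through four therapies, concludes: "we aim to include at least 19 CR clinics in our study".

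That section gives its method and inputs:

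- "Calculations were based on the normal approximation to the binomial distribution"
- "using a type I error risk (alpha) of 5% and 80% power"
- the assumption that "participating clinics will see 350 CR patients, on average, during the study period of 1 year"
- the assumption that "there will be a design effect of 23.0 due to clustering", from an intra-cluster correlation of 0.063.

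It then gives a clinic count and a patient count for each therapy. Exercise training (92.6% to 97.6%) needs 19 clinics and 6,712 patients. Education (87.6% to 95.1%) "requires 14 participating clinics (5,057 patients"). Relaxation (59.6% to 74.6%) needs ten clinics and 3,517 patients. Lifestyle change (57.4% to 72.4%) "will also require that 13 clinics (3,632 patients) participate". The counts are worded as clinics taking part in the trial, not clinics per arm. Under Study design, the two arms are each other's control.

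**The concern.** The trial size is stated as 18 in one place and as a minimum of 19 in another. Both statements are in current text and both are in the future tense. Nothing says that 18 is the number actually recruited, and no power is given for 18.

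The lifestyle clinic count also clashes with the relaxation count next to it. The two patient numbers differ by 3,632 − 3,517 = 115, about a third of one clinic, yet the clinic counts differ by three.

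A reader therefore cannot tell what size is planned or what power it has. Anyone who re-divides the patient numbers to repair this will also meet a larger question: whether those numbers describe the whole trial or one arm.

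**Working it through.** **Inputs** (all from the Sample size section): alpha 5%, power 80%, m = 350 patients per clinic, ICC 0.063, and the four pairs of proportions above. Whether alpha is one- or two-sided is not stated; two-sided is inferred because it reproduces the printed figures.

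**Step 1. Design effect.** 1 + (350 − 1) × 0.063 = 22.987, printed as 23.0.

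**Step 2. Reproduce the patient numbers.** The pooled normal approximation, without continuity correction, gives the size per arm:

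n = [1.960·√(2p̄(1 − p̄)) + 0.8416·√(p₁(1 − p₁) + p₂(1 − p₂))]² / (p₂ − p₁)²

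For exercise training, p̄ = 0.951 and n = (0.5983 + 0.2552)² / 0.05² = 291.4, so 292. Then 292 × 22.987 = 6,712, the printed figure.

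| Therapy | n per arm | n × 22.987 | Printed patients |
|---|---|---|---|
| Exercise | 292 | 6,712 | 6,712 |
| Education | 220 | 5,057 | 5,057 |
| Relaxation | 153 | 3,517 | 3,517 |
| Lifestyle | 158 | 3,632 | 3,632 |

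All four match exactly as the size of **one arm**. None matches as a two-arm total under one-sided, continuity-corrected or unpooled variants.

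**Step 3. Divide by 350.**

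| Therapy | Printed patients / 350 | Printed clinics | Two-arm patients | / 350 | Clinics, two equal whole arms |
|---|---|---|---|---|---|
| Exercise | 19.18 | 19 | 13,424 | 38.4 | 2 × 20 = 40 |
| Education | 14.45 | 14 | 10,114 | 28.9 | 2 × 15 = 30 |
| Relaxation | 10.05 | 10 | 7,034 | 20.1 | 2 × 11 = 22 |
| Lifestyle | 10.38 | 13 | 7,264 | 20.8 | 2 × 11 = 22 |

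The lifestyle 13 fits neither reading; 13 × 350 = 4,550. Starting from the section's other lifestyle figure, 54.1%, with the same +15 points, gives 164 × 22.987 = 3,770 patients, or 10.8 clinics, and 21.5 clinics when doubled. That does not give 13 either.

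The other three counts fall just short of their own patient numbers:

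- 19 × 350 = 6,650, which is 62 short
- 14 × 350 = 4,900, which is 157 short
- 10 × 350 = 3,500, which is 17 short.

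**Step 4. 18 against 19.** 18 × 350 = 6,300, which is 412 patients (6%) below 6,712.

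**Step 5. Power with the clinics split over two arms.** The effective size per arm is (clinics/2) × 350 / 22.987, which is 137.0 at 18 clinics and 144.6 at 19 (19 treated as an even split). Power is Φ{[(p₂ − p₁)√n − 1.960·√(2p̄(1 − p̄))] / √(p₁(1 − p₁) + p₂(1 − p₂))}. For exercise at 18 clinics this is Φ{(0.5853 − 0.5983) / 0.3032} = Φ(−0.043) = 0.48.

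| Therapy | 18 clinics | 19 clinics |
|---|---|---|
| Exercise | 48% | 50% |
| Education | 60% | 62% |
| Relaxation | 76% | 78% |
| Lifestyle | 74% | 76% |

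**The case against.** The strongest reply is that most of this changes nothing. Only exercise training sets the target, so correcting 14, 10 or 13 would not move recruitment. The 350 patients per clinic is an assumed average, and 6,712/19 = 353 per clinic would close the exercise gap. If the printed patient numbers are accepted as the requirement, 19 clinics give 79.7% power for exercise (formula above with n = 19 × 350 / 22.987) and even 18 give 77.5%. On that footing the 18 against 19 discrepancy costs little, and the lifestyle figure is an editorial slip.

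The part about rounding stands: those gaps are negligible and would not merit a comment alone. The rest holds only if the printed numbers are trial totals, and Step 2 shows that they are not. The two trial sizes remain unreconciled and the lifestyle count remains underivable on any reading.

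Three stronger readings are tempting, and the document does not support them:

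- A reader might infer that the correct counts are 20, 15, 11 and 11, simply by rounding the quotients up. These still treat one-arm sizes as trial totals; 20 clinics would give about 52% power for exercise.
- A reader might infer that the lifestyle count is two clinics too high (13 against 11). With two arms it is too low (13 against 22). What can be said is that 13 follows from nothing stated.
- A reader might fault the lack of an allowance for clinics excluded after the data audit. The article gives no expected exclusion rate, words 19 as a floor, and may leave such an allowance to the full protocol.

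**Conclusion.** The concern holds in this form: the article states two incompatible trial sizes, and one of its four clinic counts cannot be derived from its own inputs. Against the printed requirement, 18 clinics fall 412 patients (6%) short. The downward rounding of the other three counts is a minor point.

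The consequence is larger than these discrepancies suggest, because the patient numbers to be re-divided are single-arm sizes. At 18 or 19 clinics, power is about 48% to 50% for exercise training, the therapy that sets the target, and below 80% for all four.

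These powers assume the stated ICC, 350 patients per clinic, a two-sided 5% test and an even split of clinics. They describe a simple comparison of two proportions, not the time-by-arm interaction in the planned mixed-effect model, whose power the article's figures do not determine.

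**What to change.** - State one number of clinics in the abstract and the Sample size section. If 18 is the number recruited and 19 the target, say so.
- Correct the lifestyle count.
- Say that the patient numbers are per arm, and recompute each clinic count as patients per arm divided by 350, rounded up, then doubled: 40, 30, 22 and 22.
- If no more clinics are to be enrolled, report the achieved power for the chosen number, using the Step 5 figures or their equivalent for the planned analysis, in place of the 80% claim.

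In text this costs a few corrected figures. In substance, the stated power becomes clearly lower, most of all for exercise training, unless the number of clinics is roughly doubled.
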